### 10.2 Secondary Endpoints:

To investigate the effects of true acupuncture compared to sham acupuncture and waitlist control on the following outcome measures compared to baseline:

- a. Brief Pain Inventory-Short Form (BPI-SF) worst pain, worst stiffness (items 15 & 16), pain severity, and pain-related interference scores at 6, 12, 16, 20, 24, and 52 weeks.
- b. Western Ontario and McMaster Universities Osteoarthritis (WOMAC) index (pain, stiffness, and function) for the hips and knees at 6, 12, 24, and 52 weeks.
- c. Modified-Score for the Assessment and Quantification of Chronic Rheumatoid Affections of the Hands (M-SACRAH) (pain, stiffness, and function) at 6, 12, 24, and 52 weeks.
- d. PROMIS Pain Impact-Short Form (PROMIS PI-SF) at 6, 12, 24, and 52 weeks.
- e. Quality of life as assessed by the FACT-ES Trial Outcome Index (Version 4) at 6, 12, 24, and 52 weeks.
- f. Functional testing of the hands (grip strength) and legs ('Timed Get Up and Go') at 6, 12, 24, and 52 weeks.
- g. Analgesic and opioid use at 2, 4, 6, 12, 16, 20, 24, and 52 weeks
- h. AI adherence at 12, 24, and 52 weeks.
- i. Urine AI metabolites at 24 and 52 weeks.
- j. Serum hormone biomarkers (estradiol, FSH, LH) and inflammatory biomarkers (serum TNF $\alpha$ , IL-6, IL-12, CRP; urine CTX-II) at 6, 12, and 24 weeks.
- k. Polymorphisms in *CYP19A1*.
- l. Safety and tolerability of acupuncture.

This study will also describe adverse events, assess the association between *CYP19A1* genotype and severity of AI-related joint symptoms, and assess the adequacy of blinding and use of additional off-study acupuncture treatments.

- 10.3 Performance Status: Patients will be graded according to the Zubrod performance status scale.

| POINT | DESCRIPTION                                                                                                                                        |
|--------------|-----------------------------------------------------------------------------------------------------------------------------------------------------------|
| 0            | Fully active, able to carry on all pre-disease performance without restriction.                                                                           |
| 1            | Restricted in physically strenuous activity but ambulatory and able to carry out work of a light or sedentary nature, e.g., light housework, office work. |
| 2            | Ambulatory and capable of self-care but unable to carry out any work activities; up and about more than 50% of waking hours.                              |
| 3            | Capable of limited self-care, confined to bed or chair more than 50% of waking hours.                                                                     |
| 4            | Completely disabled; cannot carry on any self-care; totally confined to bed or chair.                                                                     |

## 11.0 STATISTICAL CONSIDERATIONS

- 11.1 The primary hypothesis of the study is that true acupuncture will decrease joint pain associated with the use of AIs in breast cancer patients compared to sham acupuncture or waitlist control at 6 weeks. Joint pain will be assessed using “worst pain” according to the BPI. Enrollees must currently be taking AIs and must exhibit joint pain with a minimum BPI worst pain score of 5; scores of 5 to 10 are considered to reflect moderate to severe pain. (149) Patients will be stratified at randomization by study site to account for potential site-specific variation in the administration of acupuncture. The primary endpoint of 6 weeks was chosen in order to confirm initial results of a 6-week acupuncture intervention given twice weekly in a larger multicenter study. (80)

The study team stipulates an  $\alpha=.025$  two-sided test (to account for two comparisons; i.e., true acupuncture vs. sham acupuncture and true acupuncture vs. waitlist control), with an estimated 5% non-adherence (reducing the nominal effect size) and 10% dropout rate (increasing the total required sample size) at the primary endpoint evaluation time of 6 weeks after randomization. In addition, the design will incorporate a 10% contamination rate (which also reduces the nominal effect size) based on the assumption that a portion of the patients will have joint pain with a different etiology (that is, not biologically associated with AI treatment and therefore not amenable to the specified intervention). The subjects will be randomized 2:1:1 to: 1) true acupuncture, 2) sham acupuncture, or 3) waitlist control. Power for the design will be a function of the difference detected and the standard deviation (SD) at 6 weeks after randomization. Data on the use of the BPI to assess joint pain from AIs is limited. A difference of 2 points in the BPI worst pain score has been identified as a clinically meaningful difference. (148) In the pilot single institution randomized sham acupuncture-controlled trial for AI-induced joint pain, the standard deviation for BPI “worst pain” at 6 weeks on the control arm was 2.31. (88) For design purposes for this multicenter acupuncture study, a more conservative estimate of standard deviation of 3.0 points will be assumed. Given the number controls in the prior study was small ( $n=18$ ), assumption of a standard deviation (SD) of 3.0 points for this study is likely conservative.

For a 2-point difference and a 3.0 point SD at 6 weeks, with other parameters as specified above, 208 total eligible patients (104 true acupuncture, 52 sham acupuncture, and 52 waitlist control) would be required for 82% power for the two comparisons, based on two separate t-tests. [Note that in power calculations, the combination of the 5% non-adherence rate and the 10% contamination rate, stipulated above, reduces the nominal effect size of a 2 point difference to 1.7 points; while the 10% dropout rate inflates the estimated sample size by a factor of 1/0.9 or about 11%.] This approach allows two fully-powered independent comparisons between true acupuncture and the two alternatives. In addition, unlike an ANOVA approach, it does not assume equal variances across the three arms, which may be more appropriate in this setting given the inclusion of a waitlist control. Power will be higher with lower observed standard deviation.

A multiple linear regression analysis of the primary endpoint will include the baseline score as well as the pre-specified stratification factor. To allow for an ineligibility of 8% (based on a recent study, [S0715](#)), a total of 228 patients will be enrolled to achieve 208 eligible patients.

The potential for different dropout by arm, especially with respect to the waitlist control, will be mitigated by monthly conferences among study investigators to encourage proper assessment and submission of forms at every required timepoint for all patients. Dropout patterns will be monitored on an ongoing basis.

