## 1.0 **OBJECTIVES**

### 1.1 Primary objective:

To determine whether true acupuncture administered twice weekly for 6 weeks (8-12 sessions) compared to sham acupuncture and waitlist control causes a significant reduction in joint pain related to aromatase inhibitors (AIs) in women with early stage breast cancer as measured by the Brief Pain Inventory-Short Form (BPI-SF) worst pain score at 6 weeks.

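### The two primary tests are valid and each has 82% power, but they share an arm and are not independent; Holm in place of the fixed 0.025 split would raise power at no cost in patients

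*Protocol*

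**What the plan says.** Section 11.1 stipulates alpha 0.025 for a "two-sided test (to account for two comparisons; i.e., true acupuncture vs. sham acupuncture and true acupuncture vs. waitlist control". It gives 208 eligible patients (104 true, 52 sham, 52 waitlist), which "would be required for 82% power for the two comparisons, based on two separate t-tests", and then states: "This approach allows two fully-powered independent comparisons between true acupuncture and the two alternatives".

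The comparators are joined in two ways. The primary objective in Section 1.1 asks whether true acupuncture "compared to sham acupuncture and waitlist control causes a significant reduction in joint pain", and the primary endpoint in Section 10.1 also joins the two controls with *and*. The primary hypothesis in Section 11.1 has pain falling "compared to sham acupuncture or waitlist control at 6 weeks". The protocol does not say whether a positive trial needs one significant comparison or both, and it names no stepwise procedure.

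**The concern.** Three things deserve attention.

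- **Independence.** Both tests use the same true-acupuncture patients, so a chance good or bad result in that arm moves both tests together.
- **What the 82% covers.** It is attached to the two comparisons jointly in the sentence, and the objective names both controls. A reader may take it as the chance of beating both. That chance is lower and is not stated.
- **Unused alpha.** If each comparison supports its own claim, a fixed 0.025 for both is stricter than family-wise control at 5% requires. Suppose true vs waitlist gives p below 0.025 and true vs sham gives p = 0.03. The stated rule calls the sham comparison negative, while a step-down rule with the same family-wise error calls it positive. Patients know when they are on the waitlist (Section 7.6a), so the sham comparison is the blinded one, and it is the comparison that would lose in this example.

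**Working it through.** **Inputs, all from Section 11.1.** Two-sided alpha 0.025 per test; SD 3.0; nominal difference 2 points; 104/52/52 eligible; 10% dropout. The plan applies "estimated 5% non-adherence (reducing the nominal effect size") and a "10% contamination rate (which also reduces the nominal effect size"), which together "reduces the nominal effect size of a 2 point difference to 1.7 points": 2 × (1 − 0.05 − 0.10) = 1.7. Evaluable patients: 104 × 0.9 = 93.6 and 52 × 0.9 = 46.8 per control arm.

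**Step 1: reproduce the 82%.**
- SE = 3.0 × √(1/93.6 + 1/46.8) = 0.537
- Standardised effect = 1.7 / 0.537 = 3.165
- Critical value at two-sided 0.025 = 2.241
- Power = Φ(3.165 − 2.241) = 82.2%; by the noncentral t, 81.5%

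The stated figure is therefore the power of one comparison.

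**Step 2: correlation of the two tests.** The shared part of the variance comes from the true arm:

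(1/93.6) / (1/93.6 + 1/46.8) = 1/3

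Under independence this would be 0.

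**Step 3: joint power under the stated split.** The two statistics are bivariate normal, each with mean 3.165, and correlated 1/3.
- P(both significant at 0.025) = 70.2%
- P(at least one) = 2 × 82.2% − 70.2% = 94.2%

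**Step 4: Holm.** Test the smaller p-value at 0.025 and, only if it is significant, the other at 0.05. Each comparison gains the cases in which its own p lies between 0.025 and 0.05 while the other is below 0.025, which have probability 4.64%.
- Per comparison: 82.2% + 4.6% = 86.9% after rounding
- Both: 70.2% + 2 × 4.64% = 79.5%

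**Step 5: if both were required.** No split is needed, because the error of declaring success is already at most 0.05 when each test is run at 0.05. The critical value is 1.960.
- Each: Φ(3.165 − 1.960) = 88.6%
- Both: 80.0%

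| Rule | Each | Both | At least one |
|---|---|---|---|
| 0.025 each (as planned) | 82.2% | 70.2% | 94.2% |
| Holm, family-wise 5% | 86.9% | 79.5% | 94.2% |
| 0.05 each, both required | 88.6% | 80.0% | not a claim |

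Holm has the same chance of at least one success as the stated split, because its first step is the same.

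**Check by simulation.** Welch t-tests, 200,000 trials, 94/47/47: 81.2% per test, 68.7% for both and 93.7% for at least one under the split; 78.5% for both under Holm; 79.1% for both at 0.05 each.

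**Sensitivity of the 70%.** The stated split is kept throughout.
- SD 2.31, the pilot value in Section 11.1: 97% per test, 94% for both.
- SD 3.0 with baseline adjustment, assuming a baseline to week-6 correlation of 0.3 to 0.5 (not given in the protocol): 76% to 86% for both.
- An assumed 2.0-point diluted effect against waitlist and 1.7 against sham, SD 3.0: 78% for both.

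**The case against.** The case for leaving Section 11.1 alone is strong on several points.

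- **The 82% is correct.** It is tied to two separate t-tests and reproduces per comparison. A reader might infer that the plan overstates its power by about 12 points (82% against 70%). The documents do not support that, because the protocol states no joint power. In the same sense, the claim that each comparison is fully powered is true.
- **The *and* is probably a list.** A reader might infer from Section 1.1 that success requires beating both controls. The same phrase introduces all the secondary objectives in Section 1.2 and the secondary endpoints in Section 10.2, where no such rule can be meant. The alpha split and the *or* in Section 11.1 point to two separate claims. On that reading the relevant figures are 82% per claim and about 94% for at least one.
- **Independence is not used.** Bonferroni controls the family-wise error under any correlation, so the shared arm does no harm to the type I error. The surrounding text contrasts the approach with ANOVA, so separate tests may be all that was meant.
- **The 70% is a low-end figure.** Section 11.1 calls SD 3.0 likely conservative, and the primary regression adjusts for baseline score.
- **Bonferroni is a legitimate choice.** It is simple and gives matching confidence intervals.

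All of this stands. Two things remain. The word independent is wrong in its statistical sense, and *and* and *or* are not reconciled, so the reader has to infer the success rule. On the two-claim reading Holm rejects whenever the stated split does and sometimes when it does not, at the same family-wise error. The protocol gives no reason for forgoing that.

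**Conclusion.** The tests are valid, the type I error is controlled and the sample size agrees with its stated purpose. What holds is narrower. The two comparisons are correlated 1/3, the 82% is per-comparison power, and the chance of winning both is about 70% under the plan's inputs. That 70% assumes the same 1.7-point effect against both controls, SD 3.0 and unadjusted t-tests; Step 5's sensitivity figures put it between 76% and 94% under the more favourable assumptions examined. On the two-claim reading, the fixed split gives up about 5 points of power per comparison and about 9 points for both, relative to Holm. This is an inexpensive improvement and a wording correction, and the trial's validity does not depend on it.

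**What to change.** In Section 11.1:

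1. Keep the two-claim reading that the alpha split implies, and replace the fixed 0.025 per comparison with Holm: the smaller p-value is tested at 0.025 and, only if it is significant, the other at 0.05.
2. Delete the word independent.
3. Label 82% as power per comparison under the present split, and add about 70% for both. Under Holm the figures are about 87% and 79%.
4. Say whether success needs one comparison or both, and align the wording in Sections 1.1, 10.1 and 11.1. If both are required, use 0.05 for each with no split (about 80% joint power) instead of Holm.

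The choice should be fixed before any outcome data are unblinded. The cost is a few sentences and no extra patients. The one drawback is that simultaneous confidence intervals are less simple under Holm than under Bonferroni.

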#### 11.2 Secondary endpoints:

- a. Secondary hypotheses (Section 10.2) will include assessment of intervention differences at each timepoint individually (weeks 6, 12, 16, 20, 24, and 52), as well as longitudinal modeling of the outcome measures over time. For longitudinal modeling, linear mixed models will be used; if there is evidence of non-random dropout, pattern-mixture models will be utilized as sensitivity analysis. Covariates for longitudinal modeling will include intervention assignment, assessment time, their interaction, baseline score, and other potential confounding variables (*i.e.* age).
- b. Exploratory analyses will also be done to evaluate the relationship between aromatase gene polymorphisms (*CYP19A1*) and inflammatory biomarkers with severity of joint symptoms and response to acupuncture treatment.
- c. A further exploratory analysis at both 6 and 12 weeks according to adherence to intervention assignment will be conducted, with receipt of  $\geq 80\%$  of planned treatment sessions defined as “adherent.” (In particular, patients will be divided into the adherent true ( $\geq 80\%$ ), non-adherent true ( $< 80\%$ ), adherent sham ( $\geq 80\%$ ), and non-adherent sham ( $< 80\%$ ) acupuncture groups.) The interaction between treatment adherence category and treatment category will be tested. Adherence to acupuncture sessions as a continuous measure will also be evaluated.
- d. The success of blinding will be evaluated by using chi-square tests to compare the percentage of patients in each group who believed that they had received true acupuncture at Weeks 6, 12, 24, and 52.

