## 6.0 **STRATIFICATION FACTORS**

Patients will be randomized using a 2:1:1 ratio to true acupuncture vs sham acupuncture vs waitlist control. Patient randomization will be dynamically balanced according to study site at time of registration.

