**SWOG PATIENT ID**

If the patient has a SWOG Patient ID assigned by a prior registration or Specimen Tracking, choose "Previous Patient" and use that number.

SWOG Patient ID Status: ☐ New Patient☐ Previous Patient:SWOG Patient ID: **DEMOGRAPHY**

Full names preferred, initials OK

Patient First Name: Patient Middle Name: Patient Last Name: **FOR SWOG INSTITUTIONS**Registrar's SWOG Roster ID Number: SWOG Investigator Number: SWOG Treating Institution Number: **PATIENT INFORMATION**Date Informed Consent Signed:  /  / Date HIPAA Authorization signed:  /  /  (Not required if Country of Residence is not USA)Projected Start Date of Treatment:  /  / **Stratification Question**

Study Site: ☐ (1) Columbia U ☐ (2) FHCRC ☐ (3) Grand Rapids CCOP ☐ (4) Kaiser Permanente NoCa  
☐ (5) Oregon HSU ☐ (6) USC

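### Section 11.2a does not list study site, the only balancing factor, among the longitudinal-model covariates; if outcomes differ by site, those secondary analyses lose a little precision

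*Protocol*

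**What the plan says.** Section 6.0 names one balancing factor: "Patient randomization will be dynamically balanced according to study site at time of registration". Section 11.1 gives the reason: "Patients will be stratified at randomization by study site to account for potential site-specific variation in the administration of acupuncture". The primary analysis follows the randomisation: "A multiple linear regression analysis of the primary endpoint will include the baseline score as well as the pre-specified stratification factor".

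Section 11.2a plans comparisons at each timepoint, "as well as longitudinal modeling of the outcome measures over time". For the latter: "For longitudinal modeling, linear mixed models will be used; if there is evidence of non-random dropout, pattern-mixture models will be utilized as sensitivity analysis". It then gives a covariate list: "Covariates for longitudinal modeling will include intervention assignment, assessment time, their interaction, baseline score, and other potential confounding variables". A closing parenthesis, introduced by i.e., contains age and nothing else. Site does not appear in that list, and no reason is given for treating it differently from Section 11.1. The covariates of the single-timepoint secondary comparisons are not stated.

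**The concern.** When arms are balanced within site, differences between sites largely cancel out of the arm comparison. A model that includes site also removes those differences from the error variance. A model that omits it does not, so its reported standard error exceeds the real sampling variability of the estimate. Intervals are then wider than necessary and tests reject less often than their nominal level.

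The two neighbouring subsections also treat the same measurement differently. BPI-SF worst pain at week 6 is the primary endpoint (Section 10.1) and also a secondary outcome (Section 10.2a). The first analysis is adjusted for site; the longitudinal one, as listed, is not. Age, which plays no part in the randomisation, is named while the balancing factor is not. What is at stake is some precision in the longitudinally modelled secondary outcomes and a consistent set of analyses.

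**Working it through.** **Inputs from the protocol.** Two-sided alpha 0.025 per comparison, 2-point difference reduced to 1.7, SD 3.0, 10% dropout, 208 eligible patients as 104/52/52, stated power 82% (Section 11.1). Six sites, from the stratification question on the Registration Worksheet in Section 18, which ends "5) Oregon HSU ☐ (6) USC".

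**Assumption.** The protocol gives no between-site variance. Let r be the share of outcome variance that site explains after the other covariates; r is varied from 0 to 15%.

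**Step 1: reproduce the plan's own figure.** The protocol gives no precision figure for the longitudinal model, so the primary design serves as the yardstick. After dropout there are 104 × 0.9 = 93.6 and 52 × 0.9 = 46.8 patients.

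- SE = 3.0 × √(1/93.6 + 1/46.8) = 0.537
- 1.7 / 0.537 = 3.165
- Power = Φ(3.165 − 2.241) = 82.2% (81.5% with the noncentral t)

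This agrees with the stated 82%.

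**Step 2: effect of omitting site.** With arms balanced within site:

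- SE ratio, without over with site = 1/√(1 − r)
- Actual size of a nominal 2.5% test without site = 2 × [1 − Φ(2.241/√(1 − r))]
- Power with site: as in Step 1 with SD 3.0 × √(1 − r)

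For r = 5%: 1/√0.95 = 1.026; 2.241 × 1.026 = 2.30; size = 2.15%.

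**Step 3: simulation check.** Six sites, 208 patients, 2:1:1 blocks within site, 10% dropout, 4,000 runs per value of r, week-6 linear model with and without site.

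| Assumed r | SE ratio, formula | SE ratio, simulated | Size of nominal 2.5% test, formula | Power with site (82.2% without) |
|---|---|---|---|---|
| 0 | 1.000 | 0.998 | 2.50% | 82.2% |
| 1% | 1.005 | 1.002 | 2.43% | 82.6% |
| 5% | 1.026 | 1.020 | 2.15% | 84.3% |
| 10% | 1.054 | 1.042 | 1.81% | 86.3% |
| 15% | 1.085 | 1.069 | 1.51% | 88.3% |

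At r = 10% the model without site reported a mean standard error of 0.534, while its estimates had a standard deviation of 0.501. This shows the overstatement directly. The simulated rejection rates have a Monte Carlo error of about √(0.025 × 0.975/4000) = 0.25 percentage points, too coarse to check the size column, so the check rests on the standard errors.

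**Step 4: bias.** The mean difference between the two models' estimates was about zero at every r. The mean absolute difference was about 0.02 to 0.06 points, against the 2-point clinically meaningful difference.

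**Limits.** The simulation uses a single visit, not the full mixed model, and its simulated baseline score was unrelated to outcome. In real data the baseline score may already absorb part of any site difference, which is why r is defined after the other covariates. The 2.5% level is borrowed from the primary endpoint; Section 11 sets no level for secondary outcomes.

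**The case against.** The strongest reply is that the list says what the covariates will include, which does not exclude site, and that the full specification of a secondary mixed model commonly sits in a statistical analysis plan, which is not at hand. This stands in part: the protocol does not forbid site, and a later plan may name it. But Section 11.2a does not defer the covariates. It lists them, and a plan that followed the list as written would omit the balancing factor.

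Several stronger readings are tempting, and the documents do not support them:

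- **That standard errors will be too wide.** This needs sites to differ in outcome. Section 11.1 speaks only of potential variation, and in how acupuncture is administered. That is not a statement that outcome levels differ between sites. The loss may be nil.
- **That the covariate set is open and can be chosen after results are seen.** The general phrase about further confounders is loosely worded, but the i.e. that follows it, read literally, limits it to age. An open set requires reading it as e.g.
- **That all secondary outcomes are affected.** The longitudinal model is used alongside single-timepoint comparisons whose covariates are not stated, and it does not fit safety or *CYP19A1* genotype.
- **That the week-6 results will conflict with the primary analysis.** The shift due to site is about 0.02 to 0.06 points on average. A mixed model over all visits can differ from a single-visit regression even with identical covariates, so adding site would not guarantee a match.

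**Conclusion.** The point holds as a minor inconsistency. The only balancing factor is in the primary regression (Section 11.1) but not in the covariate list for the longitudinal models (Section 11.2a), and the protocol gives no reason.

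The consequence is conditional and conservative. If site explains 1%, 5% or 10% of outcome variance, standard errors for the longitudinally modelled secondary outcomes are about 0.5%, 2.6% or 5.4% wider than they need be, or 0.2%, 2.0% and 4.2% in simulation. If sites do not differ, nothing is lost. These shares are assumptions, and the formula also assumes arms are balanced within site. The omission does not bias the treatment estimate or raise the false-positive rate, and the primary test and the sample size are untouched.

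**What to change.** In Section 11.2a, give the longitudinal covariates as a closed list: arm, time, arm-by-time interaction, baseline score, study site and age. This replaces the general phrase about further confounders together with its parenthesis. State that the single-timepoint secondary comparisons are also adjusted for study site, as the primary regression is.

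The cost is a line or two of text and 6 − 1 = 5 degrees of freedom. If sites turn out not to differ, the price in precision is about 0.2% of a standard error (simulated ratio 0.998 at r = 0). No new data are needed, because site is recorded at registration.
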